#### Sampling method

We will use a multistage stratified random sampling method to identify 17 urban and 17 rural primary sampling sites in 17 of the 31 province-level administrative regions (hereafter, ‘provinces’) in mainland China. The 31 mainland provinces were first stratified by China’s seven administrative regions (Northeast, North, Northwest, East, Central, South and Southwest China) and then specific provinces from all seven geographic regions were selected to be nationally representative of the economic level and population size of the 31 different provinces. The 17 selected provinces included Heilongjiang and Liaoning from Northeast China; Beijing, Hebei, Tianjin, and Shanxi from North China; Gansu, Shanxi and Xinjiang from Northwest China; Zhejiang and Shanghai from East China; Henan, Hunan and Hubei from Central China; Guangdong from South China; and Sichuan and Chongqing from Southwest China.

Within each selected province, the second stage of sampling relied on China’s Disease Surveillance Points (DSP) System, a national representative sampling frame developed by the National Health Commission of the People’s Republic of China starting in 1978 that uses a stratified cluster random sampling method to select surveillance points (i.e., geographic areas that typically includes multiple communities or neighborhoods) around the country [30]. By 2021, a total of 605 points from all 31 provinces were included in this system, with a combined population of over 300 million individuals [30]. The disease surveillance points system provides a nationally representative cohort that has been widely used in national studies about the mortality and morbidity of various diseases [31, 32]. The number of DSP in the 17 selected provinces ranged from 7 (in Tianjin, Beijing and Shanghai) to 27 (in Heilongjiang). The DSP in each province were first stratified as urban or rural (based criteria specified by the National Bureau of Statistics) and then one urban and one rural DSP was selected for each province, resulting in a total 34 DSP. The criteria for selecting DSP within a province included 1) having a mean age of community members similar to that of all urban residents or all rural residents in the province; 2) having qualified mental health providers who were willing to participate in the management of the project; and 3) availability of MRI equipment needed to conduct the imaging part of the assessment.

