#### Sample size

Based on a previous cross-sectional epidemiological study, the prevalence of major depressive disorder among adults in China was 2.1% [33]. Using version 15.0 of the Power Analysis & Sample Size (PASS) package, a sample size of 79,986 is required to identify a condition with a prevalence of 2.1% with a 95% confidence interval of 2.0% to 2.2%. We conservatively decided on a total target cohort of 85,000. This sample will be equally divided between the 34 sampled communities, that is, 2500 individuals in each community. Considering a potential non-response rate of 30% [34], the baseline recruitment will approach at least 3250 adults in each community. Individuals who are lost to follow-up after enrollment will be replaced annually by other individuals who live in the same community, maintaining the cohort size to a minimum of 2500 individuals at each primary sampling site throughout the 5 years of the project.

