
**Table 2 Tab2:** Environmental level variables at each of the 34 study communities

TYPE OF DATA Source of data Collection method	Variables
**CLIMATE** Official website of China Meteorological Administration Researchers record data for the 34 sites each season each year	1. **Temperature:** Lowest, highest, and average temperature per season
	2. **Precipitation:** Lowest, highest, and average precipitation per season
	3. **Sunshine:** Lowest, highest, and average time of sunshine per season
	4. **Climate alert:** Types and frequencies of climate alerts per season
	5. **Natural disasters**: Intensity and duration of natural disasters, including floods, forest fires, earthquakes, mud-rock flow, and typhoons
**NATURAL ENVIRONMENT** Official website and annual report of Ministry of Ecology and Environment Researchers record data for the 34 sites each season each year	6. **Noise:** Days noise level exceeds standard level, average intensity of noise, type of noise
	7. **Atmospheric environment:** Lowest, highest and average level of air pollution index (e.g., PM 2.5, SO_2_), average days air quality rated as ‘good’ or better
	8. **Water environment:** Water quality and nutrition index of main rivers and lakes
	9. **Soil environment:** Amount and quality of cultivated area
	10. **Radiation:** Intensity of ionizing radiation and electromagnetic radiation
	11. **Pollution:** Amount and type of waste discharged into the environment, including but not limited to solid waste, car exhaust, industrial waste
**SOCIOECONOMIC CHARACTERISTICS** Official website of National Bureau of Statistics and China Statistical Yearbook Researchers calculate socioeconomic indexes based on data provided in the two sources	12. **GDP index:** Total and per capita GDP
	13. **Aging index:** Proportion of population aged over 60 years old
	14. **Poverty gap** Proportion of population living below local poverty level

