#### Data analyses

Three main analyses will be conducted. P values of < 0.05 will be considered statistically significant.

The first set of analyses will describe the characteristics of participants and the detailed epidemiology of depression, including the prevalence, incidence, regional characteristics, and trends in the demographic characteristics of depression over time. Means and standard deviations will be used to describe continuous variables, and numbers and percentages will be used to describe categorical variables. Poststratification weights will be used to estimate the national prevalence and incidence of depression. Latent variable analyses and disease trajectory analyses will be used to describe the changes of depressive disorders over time.

The second set of analyses will 1) identify risk factors that influence the onset, severity and course of depressive disorders; 2) identify characteristics that can help distinguish distinct subtypes of depression; and 3) assess potential pathophysiological mechanisms that link the different types of factors associated with depression – external environmental factors, social factors, psychological factors, and biological factors. T-tests, analyses of variance, Kruskal–Wallis tests and Chi-square tests will be used to analyze differences between groups. Correlation analyses will be used to check correlations between variables. To identify potential risk factors for depression, Cox regression analyses will be used to estimate the hazard ratios (HRs) of the association of specific bio-psycho-social risk factors with the diagnosis of depression. Logistic and liner regression will be used to identify factors associated with the severity or depressive episodes. Genomic analysis (including GWAS analysis, Mendelian Randomization), metabolomic analysis and gut microbiome analysis may also be used to explore potential biological mechanisms of depression.

The third set of analyses will use the findings about risk factors to generate and test different prediction tools of depression. Different predictive models will be generated using machine learning algorithms, including Support Vector Machine, Decision Tree and Random Forest algorithms [37, 38]. Performance of the different models will be compared using the area under the receiver operating curve, prospective prediction results (sensitivity, specificity, accuracy, positive predictive value, negative predictive value) and decision curve analysis (DCA) [38].

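### None of the named risk-factor tests or models accounts for clustering in 34 communities, so nominal 5% tests of community-level exposures would have a badly inflated error rate

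*Protocol article*

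**What the plan says.** **Design.** Under Sampling method, "one urban and one rural DSP was selected for each province, resulting in a total 34 DSP". One community is then chosen within each surveillance point. Under Sample size, "This sample will be equally divided between the 34 sampled communities, that is, 2500 individuals in each community".

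**Exposures.** Table 2 is titled "Environmental level variables at each of the 34 study communities" and lists 14 numbered climate, natural-environment and socio-economic variables. Everyone in a community shares the recorded value. The Follow-up section has these variables collected annually. Table 2 adds that the climate and natural-environment items are recorded every season.

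**Analysis.** The second set of analyses under Data analyses covers environmental as well as social, psychological and biological factors. It states that "T-tests, analyses of variance, Kruskal–Wallis tests and Chi-square tests will be used to analyze differences between groups". For risk factors it states that "Cox regression analyses will be used to estimate the hazard ratios (HRs) of the association of specific bio-psycho-social risk factors with the diagnosis of depression". For severity, the named methods are linear and logistic regression. The threshold is "P values of < 0.05 will be considered statistically significant". No random effect, frailty, multilevel model, robust variance, ICC or design effect is mentioned anywhere. Poststratification weights are named, but only for the national prevalence and incidence estimates.

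**Sizing.** The article says that "a sample size of 79,986 is required to identify a condition with a prevalence of 2.1" percent. The precision sought is given as an estimate "with a 95% confidence interval of 2.0% to 2.2" percent. No allowance for clustering is described.

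**The concern.** In their standard form, all the named tests and models assume independent observations. People in one community share local conditions, services and assessors, so their outcomes are likely to be correlated. For an exposure that is the same for all 2,500 members of a community, even a very small correlation makes the usual standard error far too small, because the information comes from differences among 34 places.

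These are the study's central questions. The Introduction presents community-level exposures, and their interaction with individual characteristics, as the gap left by earlier cohorts, and the third specific aim is built on them. They are also the analyses in which an independence-based P value is least reliable.

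**Working it through.** **Inputs from the protocol article.** 34 communities with m = 2,500 each (34 × 2,500 = 85,000); threshold 0.05; 14 variables in Table 2; five years of follow-up; stated sample size 79,986 for a prevalence of 2.1% and a 95% interval of 2.0% to 2.2%.

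**Assumptions, not in the article.** Two-sided tests; ICC from 0.0005 to 0.01; incidence 0.3% to 1% per year; between-community coefficient of variation (CV) of incidence rates from 0.1 to 0.5.

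**Step 1: reproduce the stated sample size.** Solving for the n at which an exact (Clopper-Pearson) 95% interval around p = 0.021 has total width 0.002 gives 79,985.3, which rounds up to 79,986. That is an exact match using simple random sampling, with a design effect of 1.

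**Step 2: type I error for an exposure constant within community.**
- Design effect: DE = 1 + (m − 1) × ICC = 1 + 2,499 × ICC.
- True error of a nominal 5% independence-based test: 2 × [1 − Φ(1.96/√DE)].
- The CV column shows the spread of community prevalences that each ICC implies at p = 0.021: CV = √(ICC × 0.979/0.021).

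| ICC (assumed) | DE | √DE (factor by which the SE is too small) | True type I error | Implied CV of prevalence |
|---|---|---|---|---|
| 0 | 1.0 | 1.0 | 5% | 0 |
| 0.0005 | 2.25 | 1.5 | 19% | 0.15 |
| 0.001 | 3.5 | 1.9 | 29% | 0.22 |
| 0.003 | 8.5 | 2.9 | 50% | 0.37 |
| 0.005 | 13.5 | 3.7 | 59% | 0.48 |
| 0.01 | 26.0 | 5.1 | 70% | 0.68 |

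**Step 3: the same question for Cox regression.** Expected events per community are 2,500 × 5 × incidence, which is 37.5 at 0.3% per year and 125 at 1% per year. Simulation used 20,000 runs per setting, gamma-distributed community rates and an exposure unrelated to outcome. It compared the ordinary Cox score test with a community-level t test on 34 − 2 = 32 df.

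| CV of community rates (assumed) | Ordinary Cox test, incidence 0.3% to 1% per year |
|---|---|
| 0.1 | 10% to 19% |
| 0.2 | 22% to 42% |
| 0.3 | 34% to 57% |
| 0.5 | 53% to 73% |

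The community-level test kept its error between 4.7% and 5.2% in every setting.

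**Step 4: degrees of freedom.** With no other community-level terms, a site-constant exposure has 34 − 2 = 32 df. With fixed province terms (16), an urban/rural term (1), the intercept and the exposure, 34 − 1 − 16 − 1 − 1 = 15 df remain.

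**The case against.** The strongest reply is that this is a condensed article. It lists method families and gives no model formula, covariates or variance estimator for any regression. A fuller plan could specify frailty or robust variance, and silence alone would not be a finding. A reader might infer that the plan declares its 85,000 participants independent. The documents do not say so. What remains is a mismatch between what is stated and the stated design: the article does name its tests, models, threshold and weights, and the one calculation it reports uses a design effect of 1. That calculation concerns prevalence precision, so it supports the reading without proving how the risk-factor models will be fitted.

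Three further limits stand.

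- A reader might say that each community exposure has only 34 values. Seasonal recording over five years gives up to 34 × 4 × 5 = 680 site-seasons for climate and natural-environment items, and the Step 2 formula applies to exposures constant within community. The independent spatial units are nevertheless still 34, nested in 17 provinces.
- A reader might conclude that a false positive is the expected result for any given exposure. That requires an ICC of about 0.003 or more, and the documents give none.
- A reader might expect any site difference to appear as a highly significant environmental effect. It would do so only if it were large enough and aligned with the exposure. National SCID-5-CV training and the quality-control procedures also work against assessor differences.

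Most Table 1 variables are measured on individuals, and the calculated inflation does not carry over to them. They are affected only to the extent that they cluster by community.

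**Conclusion.** The point holds for community-level exposures. Followed as written, the named methods do not allow for the sampling of 34 communities, and poststratification weights for prevalence and incidence do not correct the standard errors of the risk-factor models. The true error of a nominal 5% test would be about 19% to 70% over the assumed ICC range of 0.0005 to 0.01. For Cox regression it would be 10% to 19% at a between-community CV of 0.1 and 34% to 57% at 0.3, under the assumed incidence. If each of the 14 Table 2 variables were tested once and none were truly associated, the expected number of false positives at ICC 0.001 would be 14 × 0.295 = 4.1, against 14 × 0.05 = 0.7 without clustering.

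All of these figures rest on assumed ICCs, CVs and incidence, and on exposures constant within community. The direction does not: any positive ICC inflates the error for such exposures.

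**What to change.** In the Data analyses section:

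- State that the Cox, logistic and linear models account for community, by shared frailty or a random intercept, or by cluster-robust variance with a small-sample correction.
- State that inference for Table 2 exposures is based on the 34 communities: about 32 df with no other community-level terms, about 15 df if fixed province and urban/rural terms are included.
- Specify a multilevel model for community-by-individual interactions.
- Use design-based versions of the group tests where the groups differ by community.

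The cost is analysis wording and standard software, with no new participants or data. The downside is wider intervals for community-level exposures. The change corrects standard errors. It does not remove bias from site differences in assessment that track exposure, and the text should say so.

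### The prediction tools are built and tested on risk-factor findings without confining selection to training data, and accuracy is listed as a comparison measure for a rare outcome

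*Protocol article*

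**What the plan says.** The Data analyses section describes three sets of analyses under one general threshold: "P values of < 0.05 will be considered statistically significant".

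The second set looks for factors linked to depression. For onset the tool is Cox regression: "To identify potential risk factors for depression, Cox regression analyses will be used to estimate the hazard ratios (HRs". Group comparisons and regressions for severity are also planned, and genomic, metabolomic and microbiome work may be added. No development sample or subset is named.

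The third set builds on this: "The third set of analyses will use the findings about risk factors to generate and test different prediction tools of depression". The algorithms are then listed: "Different predictive models will be generated using machine learning algorithms, including Support Vector Machine, Decision Tree and Random Forest algorithms". Models are to be compared by the area under the ROC curve and by "prospective prediction results (sensitivity, specificity, accuracy, positive predictive value, negative predictive value) and decision curve analysis (DCA"). That makes seven measures, with no primary one and no rule for choosing between models.

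On outcome frequency, the Sample size section gives only a cross-sectional figure: "the prevalence of major depressive disorder among adults in China was 2.1"%. The article gives no incidence, and no sample size for the prediction models.

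**The concern.** If predictors are picked because they are associated with the outcome, and the same people's outcomes are then used to test the model, the test is not independent. A split or cross-validation added only at the modelling stage does not cure this, because the held-out outcomes have already shaped the list of inputs. The order of work is therefore at issue, and not only an unreported split. Noise variables that passed the screen by chance would pass as predictors, and the apparent discrimination would not carry over to new communities.

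The second issue is the metric list. When few people are cases, accuracy is almost entirely the proportion of non-cases labelled correctly. It can favour a model that finds nobody over one that is clinically useful.

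Prediction is one of the article's three main analysis sets, so its performance figures will be read as a main result.

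**Working it through.** **Inputs from the article.** Cohort 85,000; prevalence 2.1%; significance threshold 0.05; 17 provinces; 36 individual-level and 14 community-level headings in Tables 1 and 2, about 50 together (several hold more than one item).

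**Inputs assumed.** The numbers of candidate predictors above 50, and a subset of 4,250 (5% of 85,000, used only as an example of a small biomarker subset). The article gives neither.

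**The plan's own figure.** The Sample size section says that "a sample size of 79,986 is required to identify a condition with a prevalence of 2.1% with a 95% confidence interval of 2.0% to 2.2"%. The simple normal formula gives 1.96² × 0.021 × 0.979 / 0.001² ≈ 78,977. The exact binomial interval at N = 79,986 has a total width of 0.0020000, so the stated figure reproduces. It concerns prevalence and says nothing about prediction.

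**Optimism from screening on everyone.** Take K independent predictors with no true effect (true AUC 0.50) and keep those with |z| > 1.96.
- Expected number kept: 0.05 × K.
- Mean z² among those kept: 5.58.
- Squared standardised separation of the linear score on the same data: D² = 0.05 × K × 5.58 × (1/cases + 1/non-cases).
- Same-data AUC: Φ(D/√2).

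With N = 85,000 there are 85,000 × 0.021 = 1,785 cases, and 1/1,785 + 1/83,215 = 0.000572. For K = 50, D² = 2.5 × 5.58 × 0.000572 = 0.0080, so D = 0.089 and AUC = Φ(0.063) = 0.525. For K = 1,000, D² = 0.160 and AUC = 0.61. With N = 4,250 there are 89 cases, and 1/89 + 1/4,161 = 0.01148. For K = 500, D² = 1.60 and AUC = 0.81.

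A simulation with 5-fold cross-validation (2 to 20 replicates per row) compared selection outside the folds with selection inside them:

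| N | Candidates | Same-data AUC, formula | Same-data AUC, simulated | Cross-validated, selection on everyone | Cross-validated, selection inside folds |
|---|---|---|---|---|---|
| 85,000 | 50 | 0.525 | 0.523 | 0.519 | 0.495 |
| 85,000 | 500 | 0.579 | 0.592 | 0.576 | 0.517 |
| 4,250 | 50 | 0.611 | 0.616 | 0.603 | 0.507 |
| 4,250 | 500 | 0.815 | 0.811 | 0.759 | 0.499 |
| 4,250 | 5,000 | 0.998 | 0.998 | 0.989 | 0.461 |

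The true value is 0.50 in every row. Selection inside the folds returns it to within simulation noise.

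**With real signal present.** Pure noise is the worst case. Assume true predictors with AUC 0.75, so d = √2 × Φ⁻¹(0.75) = 0.954, and add noise separation e. Apparent AUC is Φ(√(d² + e²)/√2). AUC in new people is Φ(d²/(√(d² + e²) × √2)).
- Noise leak 0.519 (50 candidates, 85,000 people): e = 0.067; apparent 0.751, true 0.749; optimism about 0.001.
- Noise leak 0.59 (1,000 candidates, 85,000 people): e = 0.322; apparent 0.762, true 0.739; optimism about 0.02.
- Noise leak 0.759 (500 candidates, 4,250 people): e = 0.994; apparent 0.835, true 0.680; optimism about 0.16.

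**Accuracy.** Accuracy = prevalence × sensitivity + (1 − prevalence) × specificity. At 2.1%:
- nobody labelled a case: 0 + 0.979 × 1 = 97.9%;
- sensitivity 0.80, specificity 0.80: 80.0%;
- sensitivity 0.70, specificity 0.90: 0.0147 + 0.8811 = 89.6%;
- sensitivity 0.50, specificity 0.97: 0.0105 + 0.9496 = 96.0%.

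All three informative models score below the empty rule. Over an assumed outcome risk of 0.5% to 5%, the empty rule scores 99.5% to 95.0%.

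**The case against.** The strongest reply is that the article never says which people are used for selection and which for testing. A reader might infer that both use the same whole cohort and that performance will therefore be inflated. The text supports neither as a statement of fact: the sets are described by topic, the results are called prospective, and annual follow-up with replacement of people lost would allow testing on later data. A condensed article may also leave the validation scheme to the full protocol or analysis plan. This stands, and so the point is a liability to optimism and not a demonstrated bias. It does not dispose of the matter. The word prospective introduces a list of measures and sets no cut-off, and Cox analyses of onset over five years would themselves use the later waves unless selection stops earlier.

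A second reply is that the significance threshold is general and not an entry rule for models, and that omics work is optional and described as exploring mechanisms. That is fair. The screen modelled above is one plausible route from findings to inputs. It uses independent predictors and a linear score, not the listed algorithms.

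Third, accuracy is one of seven measures. A rule that labels nobody a case has sensitivity 0, AUC 0.50 and no net benefit, so the rest of the list would expose it. A reader might infer that accuracy ranks the models; no such rule is stated. The 2.1% is also a cross-sectional prevalence of major depressive disorder, not the incidence of depressive disorders.

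**Conclusion.** The point holds in limited form. The stated order of work lets outcomes of test participants shape the model inputs, and nothing in the article confines selection to training data. The resulting optimism is small, about 0.02 AUC or less, for some 50 variables in 85,000 people. It is potentially large for high-dimensional omics or MRI features in smaller subsets. MRI is a likely instance, because scans are referred for high-risk participants and optional for the rest. The larger figures are illustrative, since candidate counts and subset sizes are assumed.

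Accuracy does not help to compare models for an outcome this rare. The 97.9% is likewise illustrative, because no incidence is given. The stronger conclusion, that the published performance will be inflated or that a useless model will be chosen, does not follow from the article. This is a cheap improvement to a stated procedure and a stated metric list.

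**What to change.** In the Data analyses section, state that predictor selection, tuning and fitting are all carried out within training data only. Estimate performance on people who played no part in selection: either leave one province out in turn across the 17, or use later waves that the risk-factor analyses did not touch. At 2 × 2,500 = 5,000 people per province, each held-out province would hold about 5,000 × 0.021 = 105 prevalent cases at the cited prevalence; incident numbers are not known. If waves or provinces are to be reserved outright, decide this before the risk-factor analyses begin.

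State that accuracy will not be used to choose between models. Report calibration (slope and observed/expected ratio) in its place, beside AUC, positive predictive value and decision curves.

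The cost is wording, some computing time and somewhat lower reported AUCs. No new data are needed.
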